## Assignment of interventions: blinding

### Who will be blinded {17a}

At baseline assessment, group allocation will be unknown to both the research assistant and the participants; treatment allocation takes place after completion of the baseline assessment by a research assistant. If people with ABI wish to be visited at home for the follow-up assessments rather than receiving the questionnaires via mail, they will be visited by a member of the research team who is blind to their treatment allocation. Blinding is not possible for the assessment of feasibility.

### Procedure for unblinding if needed {17b}

There are no foreseen circumstances under which unblinding is necessary.

## Data collection and management

### Plans for assessment and collection of outcomes {18a}

#### Feasibility

Several methods will be used to obtain information on the process evaluation outcomes: (1) registration forms for case manager activities, (2) written notes of supervision meetings, (3) responses to the questionnaires and participants’ communication with case managers derived from the ReMinder and the OZO system, (4) evaluation forms after 12 months and at study end for participants (both people with ABI and family members) receiving case management and (5) focus group interviews at study end.

##### Focus groups

Focus groups will be held to obtain in-depth information on the experiences with receiving case management (for participants) and with delivering case management (for case managers). Focus groups are group interviews (approximately 6 participants each) with a particular subject (or focus), and they make use of social interactions between participants. Focus groups are an ideal method to reveal various perspectives on a topic and to uncover new insights and unanticipated issues [75]. During the focus groups, a moderator (researcher) will use a discussion guide that will include questions on the topics based on fidelity, dose delivered, dose received, reach, recruitment and context [72]. The interviews will be audio recorded as well as video recorded, to ensure identification of potentially relevant non-verbal information or cues presented by the participants. A second researcher will take additional notes during the focus group interviews.

People with ABI and family members of the three different regions will be selected to form a sample including a wide range of injury-related characteristics and needs (purposively selected) to participate in focus group interviews at the end of the study period. In each region, one people with ABI focus group and one family member focus group will be planned (six in total). This should be sufficient to achieve saturation, i.e. when no new issues emerge from the last focus group, as research suggests that saturation is usually achieved after the fourth group discussion [75]. Saturation will be checked after these groups and if necessary, additional focus groups will be planned. Because the case managers form a limited group within the scope of the project (25–30 case managers), we aim to include all case managers in focus groups, divided in 3–4 groups.

#### Effectiveness and cost-effectiveness

The baseline assessment will be completed no more than 2 months after the visit to or discharge from the hospital or, in case of inpatient rehabilitation following hospital discharge, as soon as possible after they leave the rehabilitation centre. Ideally, assessments take place at the participants’ home, but can take place via telephone or questionnaires may be sent and returned by mail in case home visits are not possible (on time). A trained research assistant will explain the study procedures once more and collect the consent form. During home visits, participants fill out the questionnaires on their own and have the opportunity to ask questions. The research assistant will provide support when necessary, for example by reading the questions and possible answers out loud in case of reading difficulties (a common problem after stroke). Information on gender, educational level and living situation will be collected at baseline; date of birth, type and date of most recent and previous brain injuries and discharge destination will be drawn from hospital records by hospital staff. Follow-up measurements will be mailed to the participants, unless people prefer to be assisted, in which case a research assistant (blind to treatment allocation) will visit them at home.

### Plans to promote participant retention and complete follow-up {18b}

Participants will receive a five-euro gift card for each measurement (maximum of 25 euros for the complete study). For participating in the focus groups, they will receive an additional fee of ten euros (gift card).

### Data management {19}

Data will be collected on paper and then entered electronically twice by members of the research team; any discrepancies between the two entries will be resolved by the person responsible for the second entry, or by discussion with a third researcher if necessary. There are restrictions in place for entering questionnaire data based on the range of answers. Manual range checks will be performed for demographic information. An audit trail will provide with information on all activities in the electronic database. Access to electronic data is controlled by a password system, and access to original data will be restricted by storing the data in a locked cabinet (see ‘Confidentiality {27}’).

### Confidentiality {27}

Data will be handled confidentially and reporting will be coded. All participants will receive a unique identifier that cannot be used to link the data to an individual subject (i.e. CM001). Collected data and personal information will be stored separately in locked cabinets. The involved researchers from Maastricht University will safeguard the key to the code. Only the national supervisory authorities such as the Inspection for Healthcare and Youth (in Dutch: Inspectie voor Gezondheidszorg en Jeugd) will have access to the data upon request. The handling of personal data will comply with the EU General Data Protection Regulation (GDPR) (in Dutch: AVG), the Dutch Act on Implementation of the General Data Protection Regulation, and the Research Data Management Code of Conduct of Maastricht University. The data will be stored for 15 years after the end of the study.

### Plans for collection, laboratory evaluation and storage of biological specimens for genetic or molecular analysis in this trial/future use {33}

There will be no collection of biological specimens.

## Statistical methods

### Statistical methods for primary and secondary outcomes {20a}

#### Effectiveness

Multilevel modelling will be used to assess the improvement of case management participants over time compared to care as usual. Primary analysis involves entering time, group and their interaction (exposure) as fixed terms. Separate analyses will be performed to assess 24-month outcomes for the subgroup of participants for whom this data is available. Sensitivity analysis will be performed by extending the resulting models with covariates, controlling for the effects of age, gender and level of education. Covariates will be kept in the model as long as they contribute significantly to the model. Significance of the fixed regression effects will be tested using the appropriate *t*-test (*α* = .05).

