### Sample size {14}

Power calculation was based on the primary outcome measure Hospital Anxiety and Depression Scale (HADS). A study evaluating a monitoring/psycho-educational intervention in patients with possible ABI due to cardiac arrest showed to be effective in improving both anxiety and depressive symptoms with a group difference on the HADS of 3.25 points, corresponding to Cohen’s *d* effect size of 0.36 [73]. With an alpha of .05 and power value of 80%, a sample size of 194 is required to detect such between-group effect in the post-intervention measurement. This number can be adjusted for the correlation between baseline and follow-up data, since baseline measures will be entered in the model as an independent variable, by multiplying the sample size by 1 − *R*^2^ (R is the population correlation between the dependent variable (post-intervention) and the pre-intervention measurement) [74]. *R* is estimated to be at least 0.5, making the sample size 194 × (1 − 0.5^2^) = 146. Taking a drop-out rate of 30% into account, at least 209 people with ABI should be recruited. For each participating person with ABI, the family member who is or would be acting as the informal caregiver will be asked to be enrolled in the study as well. The number of participating family members will not exceed the maximum of 209.

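### The sample size takes a 25% reduction for baseline HADS as a model term, but the primary model as written does not contain that term

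*Protocol article*

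**What the plan says.** Sample size {14} plans on a standardised difference ("effect size of 0.36") and specifies the target as a sample large enough "to detect such between-group effect in the post-intervention measurement". The starting figure is given as "With an alpha of .05 and power value of 80%, a sample size of 194 is required". It is then multiplied by 1 − R², and the stated reason is "since baseline measures will be entered in the model as an independent variable". The correlation "is estimated to be at least 0.5, making the sample size 194" × (1 − 0.5²) = 146. Finally: "Taking a drop-out rate of 30% into account, at least 209 people with ABI should be recruited".

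The Effectiveness section of {20a} specifies a multilevel model: "Primary analysis involves entering time, group and their interaction (exposure) as fixed terms". Age, gender and level of education are added only in a sensitivity analysis. Baseline HADS appears in neither list. Outcomes {12} places baseline first among the assessment times, followed by 6, 12, 18 and 24 months.

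**The concern.** The two sections describe different analyses. Under {14}, baseline is a covariate that removes part of the variance of the follow-up score. Under {20a}, the natural reading is that baseline is one of the repeated outcomes, so that the time-by-group term compares change from baseline between the arms. The gain from conditioning on baseline is not the same as the gain from subtracting it, and at R = 0.5 subtraction gains nothing.

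The 146 evaluable and 209 recruited both rest on the covariate version. An analyst who follows {20a} loses the precision for which the trial was sized. One who follows {14} departs from the published primary model.

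**Working it through.** **Inputs from the Protocol article.** d = 0.36, alpha 0.05 (sidedness not stated), power 80%, R at least 0.5, drop-out 30% (all {14}); 1:1 allocation ({8}).

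**Step 1: reproduce the plan's figures.** Two-sample t-test, d = 0.36, 80% power:
- One-sided alpha 0.05: 96.09 per arm, rounded up to 97, total 194. This matches.
- Two-sided alpha 0.05: 122.09 per arm, rounded up to 123, total 246 (244 by the normal approximation). This does not match.
- 194 × 0.75 = 145.5, rounded up to 146; 146 / 0.70 = 208.6, rounded up to 209. Both match.

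So 194 is a one-sided figure, although the text does not say so.

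**Step 2: variance factors for one follow-up visit**, relative to an unadjusted comparison at that visit, assuming equal variances at baseline and follow-up:
- Baseline as covariate: 1 − R² = 1 − 0.25 = 0.75.
- Baseline as a level of time, contrast in change: 2(1 − R) = 2 × 0.5 = 1.00.

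The difference is 2(1 − R) − (1 − R²) = (1 − R)², which is never negative. For the same visit, baseline adjustment is therefore at least as precise at every R.

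**Step 3: power with 146 evaluable (73 per arm).** The noncentrality is d × √(73/2) / √v, where v is the variance factor:
- v = 0.75: 0.36 × 6.04 / 0.866 = 2.51
- v = 1.00: 0.36 × 6.04 / 1 = 2.17

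| Model, single visit, R = 0.5 | Factor | One-sided 0.05 | Two-sided 0.05 |
|---|---|---|---|
| Baseline as covariate ({14}) | 0.75 | 80% | 70% |
| Change contrast ({20a}, baseline as a level of time) | 1.00 | 70% | 58% |

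These are t-test values; the normal approximation agrees to within about one point. The missing term costs about 10 points one-sided and about 12 two-sided.

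**Step 4: sensitivity to R** (change contrast, normal approximation, one-sided / two-sided):
- R = 0.6: factor 0.80, power 78% / 68%
- R = 0.7: factor 0.60, power 88% / 80%; with baseline as covariate, 92% / 86%

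The change contrast reaches the planned factor of 0.75 at R = 1 − 0.75/2 = 0.625.

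**Step 5: sensitivity to the contrast** (R = 0.5, compound symmetry, constant effect). For the mean of three follow-ups minus baseline, the factor is 2/3 + 1 − 2 × 0.5 = 0.67, giving about 84% / 75%. With baseline as covariate, the same averaged contrast has factor 2/3 − 0.25 = 0.42, so adjustment is again the more precise.

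**Step 6: evaluable sample needed for 80% at R = 0.5, single visit.**
- Without the reduction, one-sided: 194 evaluable, 194 / 0.70 = 277.1, so 278 recruited.
- Without the reduction, two-sided (normal): 244 evaluable, 349 recruited.
- With the reduction, two-sided (normal): 244 × 0.75 = 183 evaluable, 262 recruited.

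**The case against.** The best defence is that {14} commits to baseline adjustment in plain terms and that {20a} is a condensed account. It gives no random effects, covariance structure or coding of time, so its list of fixed terms may not be exhaustive. Read together, the sections could describe a model of follow-up HADS with baseline as covariate. That possibility stands, and the article does not prove that an unadjusted model will be run. It does not remove the conflict, however. The primary model's fixed terms are stated, further covariates are named as a sensitivity extension, and baseline HADS is in neither place.

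It can also be said that the loss is conditional. R is given as at least 0.5, and above 0.625 the change contrast does better than the planned factor. An averaged follow-up contrast does so even at R = 0.5. A likelihood-based model also uses earlier visits from people who later drop out, so 73 per arm is an approximation. All of this stands and limits the size of the claim. But {14} sizes the trial for the post-intervention measurement, so the single-visit comparison at the planning R is the like-for-like one.

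A reader might infer something stronger: that the missing term takes power from the planned 80% to 54–62%. The documents do not support this. That range is the two-sided power of a linear-slope interaction over 0–18 months, and {20a} specifies neither linear time nor that contrast. It also merges two defects, because two-sided power is only about 70% even with full baseline adjustment. Nor is there bias or type I error inflation here: the unconstrained time-by-group model is valid under randomisation, and only precision is lost.

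**Conclusion.** Wrong as written: {14} and {20a} contradict each other on whether baseline HADS is a term in the primary model, and the 25% reduction depends on it. Following {20a}, with baseline as a level of time, a single-visit contrast and R = 0.5, power with 146 evaluable is about 70% instead of 80% on the one-sided basis behind 194, or about 58% instead of 70% two-sided. These figures assume equal variances over time and d = 0.36. The contradiction does not depend on them. The size of the loss does: it shrinks at higher R or with averaged follow-ups, although baseline adjustment remains at least as precise for the same contrast.

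**What to change.** In {20a}, define the primary model to match {14}: HADS at the follow-up visits as outcome; baseline HADS and baseline-by-time as covariates; time, group and group-by-time as fixed terms. Equivalently, keep baseline as an outcome and constrain the two arms to a common baseline mean.

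This takes one sentence. Baseline HADS is already collected, and before the allocation envelope is opened, so there is no added burden and no real drawback. It should be settled before outcomes are analysed by arm.

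The change restores about 80% power only on the one-sided basis. Two-sided power stays at about 70%. That is a separate defect in {14}, to be corrected by stating the sidedness and restating the figure: at R = 0.5 with baseline adjustment, 80% two-sided power needs about 183 evaluable and 262 recruited.

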## Methods: participants, interventions and outcomes

### Study setting {9}

Recruitment of people with ABI will take place between November 2019 and July 2020 in three hospitals in the Netherlands: Deventer hospital (Deventer), St. Antonius hospital (Nieuwegein and Woerden) and Flevo hospital (Almere). Hospital staff will recruit people with ABI without further involvement in the study procedures, assessments will take place through home visits, via telephone or by sending questionnaires via mail.

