### Outcomes {12}

#### Effectiveness

Outcomes measures were chosen according to the aim of case management, which involves the concepts of psychosocial well-being, self-efficacy and (unmet) needs. Assessment will take place at baseline, after 6, 12, 18 and 24 months. The total score of the Hospital Anxiety and Depression Scale (HADS [51];) will serve as the primary outcome measure, other measures (see below) are secondary outcomes.

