### Participant timeline {13}

The schedule of enrolment, interventions and assessments can be found in Table 1. All participants will receive the study questionnaires every 6 months until December 2021. Depending on the time of inclusion (up to June 2020), people with ABI will be followed up for 18 to 24 months. A subsample of people with ABI and family members will be approached for additional participation in focus group interviews, taking place at the end of the study (between October and December 2021).The evaluation form will be sent after 1 year and at the final measurement, which can be 18 or 24 months after baseline assessment depending of the time of enrolment.

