## Discussion

It is essential that people with ABI are supported in learning how to live with ABI, within the individual context in terms of home, education, work, relationships, stage of life and personal goals [14]. Creating a continuous chain of support from hospital discharge onwards is high on the agenda of guidelines and action plans for different types of ABI [12–15]. Continuous and long-term support is currently lacking, as is evident from numerous studies reporting this an important unmet need for people with ABI and caregivers [9–11] and the lack of randomized controlled trials on longer-term care. We respond to this issue by developing and evaluating case management for people with ABI and their family members. We will evaluate whether case management for ABI is feasible, effective and cost-effective compared to care as usual with a randomized controlled trial.

Strengths of the study are the pragmatic nature of the study and the long-term follow-up. The follow-up with a maximum of 24 months approximates the time it usually takes for people to regain a balance in their lives [10]. Furthermore, the pragmatic nature allows us to evaluate case management the way it could be implemented in regular practice. The use of the monitoring tool (the ReMinder) is another strength, as it takes a minimum amount of time and effort to keep track of a large group of people for long periods of time. Finally, the combination of qualitative and quantitative evaluation methods should provide us with rich data on feasibility, effectiveness and cost-effectiveness.

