## Trial status

The Medical Ethics Committee of Maastricht University Medical Center+ granted ethics approval of the third version of the protocol on September 17, 2019. The trial was registered at the Netherlands Trial Register (registration number NL8104, https://www.trialregister.nl/trial/8104) on October 22, 2019, after which recruitment started. The first person was enrolled on November 25, 2019. Inclusion is currently ongoing and expected to be completed in September 2020.

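### On the protocol's own dates only baselines up to 31 December 2019 can reach month 24, so the separate 24-month subgroup test is too small to support a 2-year conclusion

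*Protocol article*

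**What the plan says.** **Assessment times.** Outcomes {12}, Effectiveness: "Assessment will take place at baseline, after 6, 12, 18 and 24 months".

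**Close of data collection.** Participant timeline {13}: "All participants will receive the study questionnaires every 6 months until December 2021". The same section counts the final measurement from the baseline assessment and makes its timing depend on enrolment: "Depending on the time of inclusion (up to June 2020), people with ABI will be followed up for 18 to 24 months".

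**Start and end of inclusion.** Trial status: "The first person was enrolled on November 25, 2019". The end of inclusion is given as June 2020 (Participant timeline), as July 2020 in Study setting {9} ("Recruitment of people with ABI will take place between November 2019 and July 2020 in three hospitals in the Netherlands") and as September 2020 in Trial status ("Inclusion is currently ongoing and expected to be completed in September 2020").

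**Analysis.** Statistical methods {20a}, Effectiveness, makes the primary analysis a multilevel model with time, group and their interaction, and tests fixed effects at alpha .05. It then adds: "Separate analyses will be performed to assess 24-month outcomes for the subgroup of participants for whom this data is available".

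**Use of the 24-month horizon.** The title describes a 2-year trial. The Discussion counts long-term follow-up among the strengths: "The follow-up with a maximum of 24 months approximates the time it usually takes for people to regain a balance in their lives". No section gives the expected size of the 24-month subgroup.

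**The concern.** The calendar leaves little room for a 24-month visit. Data collection closes about 25 months after the first enrolment, while enrolment runs for 7 to 10 months, so only the earliest enrolees can complete 24 months. The plan nevertheless sets up a separate analysis of that subgroup under the same alpha as everything else, does not call it exploratory and gives no expected n.

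The stake is how the 2-year result will be read. A non-significant result with very low power could be taken as absence of a 2-year effect. A significant one would need an observed difference far above the planned one and would probably exaggerate the true effect. If the separate analysis uses only people with 24-month data, it also ignores the earlier visits of everyone else, which the multilevel model already chosen could use.

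**Working it through.** **Inputs.** From Sample size {14}: 209 to be recruited, 30% drop-out, alpha .05, power 80%, d = 0.36 (3.25 HADS points), R = 0.5. Allocation is 1:1. The dates are those quoted above. Not stated, and therefore assumed: uniform accrual from 25 November 2019, no tolerance around the 24-month visit, and close of collection on 31 December 2021.

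**Step 1, the protocol's own figures.** A two-sample t-test with d = 0.36, alpha .05 and 80% power gives 194 in total if one-sided and 246 if two-sided, so the stated 194 corresponds to a one-sided test. Then 194 × (1 − 0.5²) = 145.5, rounded to 146, and 146 / 0.70 = 208.6, rounded to 209. The chain is reproduced.

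**Step 2, latest usable baseline.** 31 December 2021 minus 24 months is 31 December 2019. From 25 November to 31 December 2019 inclusive is 37 days.

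**Step 3, people able to reach month 24.** Enrolled in window = 209 × 37 / accrual days; retained = 0.70 × enrolled.

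| Inclusion ends | Accrual days | Share | Enrolled in window | Retained |
|---|---|---|---|---|
| 30 June 2020 | 219 | 16.9% | 35.3 | 24.7 |
| 31 July 2020 | 250 | 14.8% | 30.9 | 21.7 |
| 30 September 2020 | 311 | 11.9% | 24.9 | 17.4 |

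So about 17-25 people in both arms together, against 146 in the sample-size calculation.

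**Step 4, power and precision.** Two-sided t-test at .05, N/2 per arm, standardised effect 0.36 / √0.75 = 0.416. The implied SD is 3.25 / 0.36 = 9.03 HADS points. The 95% CI half-width is 1.96 × √0.75 × 9.03 × √(2 / (N/2)).

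| N in both arms | Power | d detectable with 80% power | 95% CI half-width (HADS points) |
|---|---|---|---|
| 17 | 12.7% | 1.26 | 7.4 |
| 22 | 15.3% | 1.09 | 6.5 |
| 25 | 16.9% | 1.01 | 6.1 |

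The planned difference is 3.25 points, about half the half-width.

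**Step 5, sensitivity.**
- January 2020 baselines also count (68 days): 45.4, 39.8 or 32.0 retained for the three end dates. Power is 21% at N = 32 and 28% at N = 45.
- Accrual counted from 1 November 2019, against the stated first enrolment: 26.6 to 36.7 retained. Power is about 18-23%.
- One-sided alpha .05, the convention that reproduces 194: 20% at N = 17 and 26% at N = 25.
- Inclusion to the end of September 2020 and collection extended to 31 March 2022 so that everyone reaches 18 months (not in the document): 128 days, 209 × 128 / 311 = 86 enrolled and 60 retained. Power is 35%.

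No scenario comes near 80%.

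**The case against.** **The main analysis is untouched.** This stands. A reader might infer that the trial's primary result rests on a couple of dozen people. The document does not support that: the multilevel model over time is primary, the 24-month analysis is an addition, and the sample-size section does not claim power at month 24. The text does not say that month 24 is left out of the primary model either.

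**The restriction is disclosed.** This largely stands. The abstract and the Participant timeline give follow-up as 18 to 24 months, the Discussion lists that time frame as a limitation (for costs), and the 24-month analysis is openly for a subgroup. No confirmatory 24-month claim is promised. What is missing is an exploratory label and an expected n for a test run at the ordinary alpha.

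**Bias is limited.** This stands. A reader might see the 24-month comparison as a biased completers-only analysis. But whether month 24 is reachable depends mainly on enrolment date, which is fixed before randomisation, and blocks of six keep the arms close to balanced among early enrolees. The cost is in precision and generalisability. Only drop-out within the early cohort is selection after randomisation.

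**The count is an estimate.** This stands. Uniform accrual is not stated and no visit window is given. A faster start, a visit tolerance or a later closing date raises the number; a slower start lowers it. The figure of 17 also pairs a September 2020 end of inclusion with a December 2021 close, which would not allow even 18 months for the last enrolees. The cut-off date is firm and the count is not, but every variant tried leaves low power.

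**Conclusion.** The point holds as a limit on what the separate 24-month test can show. The cut-off of 31 December 2019 follows directly from the protocol's dates and leaves 12-17% of the enrolment period. With uniform accrual of 209 people and 30% drop-out, about 17-25 people would give 24-month data, and two-sided power for d = 0.36 is about 13-17%. With a one-month tolerance it is about 32-45 people and power stays below 30%. Such a test cannot support a 2-year conclusion in either direction. This is a matter of precision, generalisability and labelling; it does not put the validity of the primary analysis in question. It should be changed, because the plan already contains the model that would do better.

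**What to change.** In Statistical methods {20a}, Effectiveness, replace the separate 24-month subgroup test with a month-24 group contrast from the single multilevel model, with time as a categorical factor and all randomised participants included. Report that contrast with its 95% CI and the number of people observed at month 24, label it exploratory, and state that effectiveness conclusions rest on 18 months.

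Because 18 months then carries the conclusions, the three end-of-inclusion dates need to be reconciled with the December 2021 close. With uniform accrual to 30 September 2020, 209 × 92 / 311 = 62 people would enter after June 2020 and could not reach 18 months in time.

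The change is to wording and model specification, with no added participants or visits. The sponsor gives up a stand-alone 24-month significance claim. The joint estimate relies on missing at random and still draws on few month-24 observations, so its interval will remain wide. Retitling the trial is optional.
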